## Abstract

**Background:**

Providing e-learning modules can be an effective strategy for enhancing gatekeepers’ knowledge, self-confidence and skills in adolescent suicide prevention. The aim of this study was to test the effectiveness of an online training program called *Mental Health Online* which consists of eight short e-learning modules, each capturing an important aspect of the process of recognition, guidance and referral of suicidal adolescents (12–20 years). The primary outcomes of this study are participant’s ratings on perceived knowledge, perceived self-confidence, and actual knowledge regarding adolescent suicidality.

**Methods/Design:**

A randomized controlled trial will be carried out among 154 gatekeepers. After completing the first assessment (pre-test), participants will be randomly assigned to either the experimental group or the waitlist control group. One week after completing the first assessment the experimental group will have access to the website *Mental Health Online* containing the eight e-learning modules and additional information on adolescent suicide prevention. Participants in both conditions will be assessed 4 weeks after completing the first assessment (post-test), and 12 weeks after completing the post-test (follow-up). At post-test, participants from the experimental group are asked to complete an evaluation questionnaire on the modules. The waitlist control group will have access to the modules and additional information on the website after completing the follow-up assessment.

**Discussion:**

Gatekeepers can benefit from e-learning modules on adolescent suicide prevention. This approach allows them to learn about this sensitive subject at their own pace and from any given location, as long as they have access to the Internet. Given the flexible nature of the program, each participant can compose his/her own training creating an instant customized course with the required steps in adolescent suicide prevention.

**Trial registration:**

Netherlands Trial Register NTR3625

## Background

Suicide is the second leading cause of death among adolescents in the Netherlands, affecting an average of 50 adolescents every year
[1]. In addition, each year, 11.2% of Dutch adolescents have suicidal thoughts and 6.6% attempt suicide or engage in deliberate self-harm
[2]. Ethnic minorities, especially Hindustan-Surinam and Turkish adolescents more often report suicidal thoughts and attempts compared to their Dutch peers
[3,4]. This is alarming since 23.5% of the Dutch adolescent population (0–20 years) consists of ethnic minority groups, the three biggest ethnic minority groups in the Netherlands being of Moroccan (15.6%), Turkish (14.1%), and Surinamese (9.8%) origin
[1]. Despite fluctuations, the Dutch suicide numbers have stayed stable over the past decade
[1], and until recently the state of available suicide prevention programs was still unclear. Therefore, in 2009 the Dutch government assigned a group of experts the task of preparing an overview of all the suicide prevention and intervention programs in the Netherlands
[5]. This inventory led to several recommendations on how to improve suicide prevention in the Netherlands. One of the advices was to educate gatekeepers involved in adolescent suicide prevention with special attention for ethnicity.

In this paper gatekeepers are defined as professionals who, due to their profession, come into contact with adolescents who may be at risk for suicide, such as school staff, youth nurses, and primary health care providers
[6,7]. According to several sources, these professionals can play an essential role in early recognition, guidance, and referral of suicidal adolescents
[6,8]. Moreover, research conducted in this area shows that gatekeeper training is a promising tool in improving suicide prevention
[9-13]. If trained properly, gatekeepers can be among the first to perceive changes in the behavior and attitude of the adolescent in need. Thus, effective training of gatekeepers seems a worthwhile investment. However, two important factors tend to keep gatekeepers from attending face-to-face training sessions on suicide prevention. First, suicide is a topic surrounded by social stigma and taboo
[6] which makes suicide a sensitive subject for potential gatekeepers to address in general. Second, most gatekeepers have busy schedules and have limited time and resources to attend face-to-face training sessions
[13,14]. Notwithstanding these issues, the Dutch government is giving gatekeepers more responsibilities when it comes to the welfare of children and adolescents. Thus, gatekeepers are required to receive training in different mental health matters that are common among adolescents, while this usually constitutes a task addition to their main duties. As a result, there is a need for time and resource-saving methods of training for these gatekeepers.

As an answer to this need, in 2011 the departments of Developmental Psychology and Clinical Psychology at VU University Amsterdam started a government-funded program called *Mental Health Online*, which aims to enhance suicide prevention among adolescents (12–20 years). The main objective of this program is to educate gatekeepers in adolescent suicide prevention through e-learning modules, defined as packed pieces of information that transfer knowledge to the learner through a web-based structure
[15]. The online character of the training is expected to create a low threshold to educate gatekeepers on this topic and is time-saving at the same time. Furthermore, recent data show that at least 94% of the Dutch households have access to the Internet and 86% of Internet users go online daily or almost daily
[1]. Thus, by offering the training online, several practical barriers that prevent gatekeepers from attending face-to-face training on adolescent suicide prevention might be overcome.

### Aims and hypotheses

The aim of this study is to develop and test the effectiveness of e-learning modules that educate gatekeepers in adolescent suicide prevention. It is expected that the e-learning modules will improve the knowledge of gatekeepers regarding adolescent suicidality (defined as suicidal behavior, i.e., ideation and actions) and that the gatekeeper’s self-confidence in interacting with suicidal adolescents will increase.

## Methods

### Study design

This study is a randomized controlled trial with two arms: an experimental group and a waitlist control group. Participants from both groups will complete three assessments: at baseline (pre-test, T₀), four weeks after completing the first assessment (post-test, T₁), and 12 weeks after T₁ (follow-up, T₂). Participants will be assigned to one of the two groups (experimental or waitlist control group) after completing the baseline assessment. The difference between the two groups is that participants in the experimental group will have access to the e-learning modules and additional information on the website *Mental Health Online* (http://www.MentalHealthOnline.nl) seven days after completing the first assessment, while participants in the waitlist control group have to wait until the follow-up assessment is completed.

The assessments consist of three questionnaires which measure the perceived knowledge, the perceived self-confidence, and the actual knowledge of participants in both groups regarding adolescent suicidality. By comparing the questionnaire information obtained from the two groups during the three assessments it is tested whether the perceived knowledge, the perceived self-confidence, and the actual knowledge of participants in the experimental group improves more than in participants in the waitlist control group after gaining access to the e-learning modules and additional information on the website.

The study protocol for *Mental Health Online* has been approved by the Medical Ethics Committee of the VU University Medical Centre Amsterdam (registration number 2009/328).

### Participants

All Dutch speaking professionals who work with adolescents are eligible to participate in this study. Inclusion criteria are that gatekeepers should i) be 18 years and older, ii) work regularly with adolescents from 12 to 20 years and be directly responsible for their (mental) healthcare, and iii) they must have access to the Internet.

Although all gatekeepers who meet the inclusion criteria are allowed to participate in the study, the following groups of professionals have been identified as the main target groups of this study: members of mental healthcare teams in schools, youth nurses, and mental healthcare employees.

### Interventions

The experimental group will have access to the restricted area of the website *Mental Health Online* (http://www.MentalHealthOnline.nl) which is especially designed for the participants of this study and which contains eight e-learning modules and additional information on adolescent suicide prevention. Each module captures an important aspect of the process of recognition, guidance, and referral of adolescent suicidality (Additional file
1). The modules are based on the Question, Persuade and Refer (QPR) Gatekeeper Training which has gained worldwide recognition when it comes to training gatekeepers in suicide prevention. The QPR model has been created by Paul Quinnett in 1995
[8]. It is composed of several essential steps in suicide prevention: early recognition of the warning signs associated with suicidality, asking direct questions regarding the suicidal thoughts, feelings, and plans of the person who might be in a suicidal state, and starting a conversation persuading the person to accept a referral for help. Research regarding the effectiveness of gatekeeper training in general is limited, but the available research on the QPR gatekeeper training is promising. Gatekeepers receiving the QPR training show improvements in knowledge about suicide prevention, skills, and self-efficacy
[16-18].

The modules have been developed by the researchers in this study in collaboration with national and international experts in suicide prevention. The modules are presented using Adobe Presenter 7 software to convert PowerPoint slides into e-learning modules. Each module takes up to 10 minutes to complete and contains voice-over, cases, and quizzes. The modules have been designed in a way that the participant controls every aspect of the module such as skipping or replaying a slide and switching the voice-over on or off. Moreover, by offering the program in eight separate modules gatekeepers have the opportunity to compose a custom-made training for themselves based on their own personal experiences and needs. However, since the amount of modules each participant follows could influence the scores on the questionnaires, a user-tracking system has been enabled on the website. With this system, data will be collected regarding the amount of modules each participant follows between the pre- and post-test, and post-test and follow-up.

Besides the modules, participants also will have access to additional information regarding adolescent suicidality on the website, such as literature and documentaries on suicidality written in Dutch, but also links to other relevant websites that contain information on (adolescent) suicidality. Furthermore, participants will have access to an online discussion board on the website which gives them the opportunity to exchange thoughts with each other, but also to consult a group of experts regarding adolescent suicidality.

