To assess the last primary outcome, actual knowledge, six cases have been developed. Each case starts with a photo of and some characteristics about an imaginary adolescent (name, age, and education are added), and is followed by three informational segments. The segments provide information about the background, friends, and family circumstances of the adolescent. After reading each case, the participant is asked to answer several questions on potential suicidality of which two are general questions (yes/no) and eight questions with multiple choice answers of which one is correct, covering the content of each of the eight e-learning modules. The number of questions the participant has to answer depends on the answers given on the general questions. During each assessment (T₀, T₁, T₂) participants will be presented with two new cases.

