### Sample size

Sample size calculation was performed using STATA version 8.2. Based on a power of 0.80 with a two-sided α of 0.05 and assuming a mean standardized effect size of (Cohen’s *d*) 0.45 a total of 154 participants are needed, 77 participants in the experimental group and 77 participants in the waitlist control group. Due to a lack of studies in this area, the standardized effect size used to calculate the sample size for this study is not based on previous studies or a pilot study. As an alternative, a moderate effect size has been estimated.

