### Assessments

Within four days after completing the baseline assessment the participants receive an e-mail from the researcher regarding the group they are assigned to and are informed on which day they will receive the second assessment. Additional to this information, those in the experimental group receive a personal username and password to log in to the website *Mental Health Online* and are informed regarding the exact period (14 days) during which they have access to the website. An instruction to the website is also attached to this e-mail.

Four weeks after completing the first assessment participants from both groups receive the second assessment (post-test), and 12 weeks after completing the second assessment the third assessment (follow-up) will be sent to the participants.

The three assessments which consist of the three questionnaires (including the evaluation questionnaire) are sent to the participants as a complete package online, and data collection is performed online.

Participants from the experimental group will regain access to the modules and additional information on the website after completing the second assessment until one week prior to the last assessment. This way, participants from the experimental group can return to the website to refresh their knowledge, follow modules they did not follow during the 14 days they had access to the website, and use the additional information and the online discussion board on the website. The reason behind making the website accessible during this relatively long period has to do with the online character of the program. By providing the modules online, we can create a low threshold to the training which is accessible to gatekeepers 24/7.

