### Recruitment

Several recruitment strategies are going to be used to recruit gatekeepers to participate in this study. First, education partnerships representing high schools in different regions and community colleges are going to be contacted by e-mail. In this e-mail, a brief summary about the study will be presented and a flyer about the research will be attached. Further, a link to the website *Mental Health Online* is included, where up-to-date information regarding the study is available. The partnerships are asked to distribute this e-mail among their members. Second, informational websites targeting gatekeepers are going to be contacted and will be asked to put a brief summary about this study on their website with a link to the website *Mental Health Online* for those interested in this study. Third, study coworkers will recruit participants during different seminars and conferences visited by gatekeepers. Fourth, a press release will be distributed by VU University Amsterdam containing information about this research and ways of contacting the study’s researchers. Finally, social media, such as Twitter and Facebook, will be used to recruit gatekeepers. Moreover, all institutes that are interested are given the opportunity to invite the researcher performing the study to give a short presentation at their institute about this study. The recruitment starts in September 2012 and the inclusion continues until September 2013.

All gatekeepers who are willing to participate in this study are required to send an e-mail to [contact] containing the following information: name, position, name of the institute the gatekeeper is employed at, and their email address. The application instructions are given on the website, in the recruitment flyer, and at the end of each presentation given on location by the researcher. After enrollment each participant receives a confirmation email containing a brief summary about the study: purposes, procedure, contact information of the researcher, and the date on which the questionnaire for the first assessment will be sent.

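### Under the access schedule, people who have already sat the case test share one discussion board with experimental participants who have not, so any talk of the cases could bias actual knowledge at T1 and T2

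*Protocol article*

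**What the plan says.** All references are to the protocol article.

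- **Interventions.** The board is part of the restricted website: "participants will have access to an online discussion board on the website which gives them the opportunity to exchange thoughts with each other". A group of experts can also be consulted there. User tracking is described for the number of modules followed.
- **Study design and Assessments.** Experimental participants get access "seven days after completing the first assessment" and "are informed regarding the exact period (14 days) during which they have access to the website". T1 is sent four weeks after baseline and T2 twelve weeks after T1.
- **Assessments.** After completing T1, the experimental arm regains the website until one week before T2. One stated purpose is that they can "use the additional information and the online discussion board on the website". Waitlist participants receive a username and password once they have completed T2, and not before.
- **Randomization and Recruitment.** People are randomised one at a time as each completes baseline. "The recruitment starts in September 2012 and the inclusion continues until September 2013".
- **Primary outcome measures.** Actual knowledge is measured with six constructed cases. At each assessment "participants will be presented with two new cases". Each case shows a photo, name, age and education, and its multiple-choice questions have one correct answer.

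**The concern.** A knowledge test built on a few fixed, recognisable cases stays fair only if both arms meet the cases equally unprepared. Here the schedule puts people who have just sat a test on the same board as people who have yet to sit it, and among those still to be tested only the experimental arm can read it. Two routes follow:

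- **T1:** experimental participants who have completed T1 post while later experimental participants are in their first access window.
- **T2:** waitlist participants who have completed T2 log in while later experimental participants still have their renewed access.

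Each assessment uses two cases, so one discussed case is half of that test. Actual knowledge is also the only primary outcome that is not a self-rating. A score raised by foreknowledge of a case would count as a training effect. Neither intention-to-treat analysis, ANCOVA nor multiple imputation could remove it, because the distortion lies in the measurement of one arm.

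**Working it through.** **1. The plan's own figure.** Inputs from Sample size: "Based on a power of 0.80 with a two-sided α of 0.05", and d of "0.45 a total of 154 participants are needed, 77 participants in the experimental group and 77 participants in the waitlist control group". Normal approximation: n per arm = 2 × ((1.960 + 0.842)/0.45)² = 77.5. Power at 77 per arm is 0.797. The planned 154 reproduces within rounding and is not affected by this point.

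**2. Access windows, in days from a participant's own baseline, assuming assessments are completed on schedule.**

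| Event | Day |
|---|---|
| Experimental, first access | 7 to 7 + 14 = 21 |
| T1 | 28 |
| Experimental, renewed access | 28 to 28 + 84 − 7 = 105 |
| T2 | 28 + 84 = 112 |
| Waitlist login | from 112 |

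**3. Entry lag needed for a leak.**
- T1 route: an earlier experimental participant can post from day 28, and a later one can read until day 21. The lag must exceed 28 − 21 = 7 days.
- T2 route: an earlier waitlist participant can post from day 112, and a later experimental participant can read until day 105. The lag must exceed 112 − 105 = 7 days.
- Waitlist participants reading the board before their own T1 or T2: not possible under the schedule.

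**4. How often the opportunity arises.** Assume even entry over 365 days, 77 per arm, no dropout, and posts that stay visible.
- Share of the experimental arm with at least one earlier experimental participant past T1 before their own first access closes: 1 − 7/365 − 1/77 = 0.968. With entry over 180 days: 1 − 7/180 − 1/77 = 0.948.
- Mean number of such earlier participants: 76 × (358/365)²/2 = 36.6.
- Mean number whose renewed access overlaps the reader's first window (lag between 7 and 98 days): 76 × [(358/365)² − (267/365)²]/2 = 16.2.
- T2 route, at least one waitlist participant past T2 before the reader's renewed access closes: 1 − 7/365 − 1/78 = 0.968.

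These figures count overlapping access only. They say nothing about posts written or read.

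**5. What a leak would do.** If a share f of the experimental arm reads case content and gains g SD, the bias is f × g SD. With SE = √(2/77) = 0.161, the two-sided rejection rate under no true effect is Φ(−1.96 − bias/SE) + 1 − Φ(1.96 − bias/SE). Both f and g are assumptions; the article gives neither.

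| f | g (SD) | Bias (SD) | Share of d = 0.45 | False-positive rate |
|---|---|---|---|---|
| 0.10 | 0.2 | 0.02 | 4% | 5.2% |
| 0.10 | 0.5 | 0.05 | 11% | 6.1% |
| 0.25 | 0.5 | 0.125 | 28% | 12.1% |
| 0.10 | 1.0 | 0.10 | 22% | 9.5% |

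**The case against.** The strongest reply is that nothing in the article shows case content reaching the board. Board settings, moderation and confidentiality wording are operational details that an article commonly leaves to the full protocol. This stands: silence on these matters is not a defect, and the point does not rest on it. It rests on the access schedule that the article does state. If board rules exist, confirming them closes the matter.

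The other objections stand in part:

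- **The board is part of the intervention.** Learning from peers and experts is a genuine effect. Only foreknowledge of a specific test case is bias.
- **The direction is not certain.** The article does not say that participants are shown correct answers, and a post from someone unsure of a case may be wrong. An advantage to the experimental arm is the most plausible direction but is not established.
- **Recall would fade.** First access closes about a week before T1, and renewed access a week before T2. This limits the gain but does not remove it.
- **Case pairs may be rotated.** The article does not say. Rotation would spread exposure across assessments without removing it, since the pool is six cases.

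A reader might also infer that waitlist participants never see the board and that T2 is therefore safe. The Assessments section does not support this, because it gives them a website login after T2, while later experimental participants still have access before theirs.

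**Conclusion.** The route for contamination is in the text, for T1 through renewed experimental access and for T2 through the waitlist logins. It can reach only one arm's untested participants and affects only actual knowledge by this mechanism. The other two primary outcomes repeat the same self-rated statements, which have no correct answer to pass on.

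The size is unknown and may be small. An illustrative 10% exposed with a 0.5 SD gain gives 0.05 SD and a false-positive rate of about 6%.

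A reader might infer from the 97% overlap that nearly the whole experimental arm is contaminated, or take the larger rows of the table as expected inflation. The documents support neither: the overlap is opportunity, not exposure, and a 1 SD gain from reading a post would be extreme. The case for acting is that the route is one-sided and cheap to close. It does not rest on a demonstrated bias.

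**What to change.** 1. **Separate the board by assessment stage.** Participants who have not completed T1 should not see posts by those who have, and likewise for T2. Keep waitlist users who have completed T2 in an area of their own.
2. **If the software cannot do this,** state on every assessment and in the board rules that test cases must not be discussed, and have the experts already on the board remove such posts.
3. **Before allocation is merged with scores,** check the board archive for discussion of the six cases, by description and not by name alone. If one case of an assessment was discussed, rescore that assessment without it in both arms as a sensitivity analysis. If both were, no clean score remains, and the result for that assessment should be reported as possibly contaminated.

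The cost is a forum setting or one line of rules, a little moderation, one archive check and slightly restricted discussion. A score rescored on one case is less precise, so it serves as a sensitivity analysis only. The randomised comparison and the sample size are unchanged.
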